## Abstract

**Background:**

Previous psychological and pharmacological interventions have primarily focused on depression disorders in populations with cardiovascular diseases (CVDs) and the efficacy of anxiety disorder interventions is only more recently being explored. Transdiagnostic interventions address common emotional processes and the full range of anxiety and depression disorders often observed in populations with CVDs. The aim of CHAMPS is to evaluate the feasibility of a unified protocol (UP) for the transdiagnostic treatment of emotional disorders intervention in patients recently hospitalized for CVDs. The current study reports the protocol of a feasibility randomized controlled trial to inform a future trial.

**Discussion:**

CHAMPS is designed to evaluate the UP for the transdiagnostic treatment of emotional disorders targeting emotional disorder processes in a CVD population. The design will provide preliminary evidence of feasibility, attrition, and satisfaction with treatment to design a definitive trial. If the trial is feasible, it opens up the possibility for interventions to target broader emotional processes in the precarious population with CVD and emotional distress.

**Trial registration:**

ACTRN12615000555550, registered on 29/05/2015

## Background

Depression disorders are severely disabling and common in cardiovascular disease (CVD) populations and portend poorer cardiovascular outcome [1, 2] and high costs [3]. Consequently, the treatment of depression disorders has dominated the contemporary psychological intervention landscape in populations with CVD for the past 25 years. Considering that depression is a putative CVD risk factor that is also modifiable, a common hypothesis is that psychosocial interventions in this population would lead to significant benefits to an otherwise poorer cardiovascular prognosis. However, prior intervention efforts addressing depressive symptoms among CVD patients have not typically produced a sizeable clinical impact upon either depression or major CVD morbidity [4], and these unsatisfying findings raise the question of how existing interventions could be improved.

Several lines of evidence indicate that interventions focusing solely on depressive symptoms in CVD patients may be too narrow in focus. Specifically, an accumulating body of work shows that anxiety disorders confer CVD morbidity risk independent of or in conjunction with depression [5–14]. Indeed, the clinical reality of comorbid depression and anxiety that is evident in CVD populations [15] closely parallels findings in clinical and epidemiological samples [16, 17]. Nonetheless, the heightened CVD risk is not constrained to simply depression and anxiety disorders given that positive associations between CVD events have been reported in relation to hostility, anger, stress, social isolation, worry, rumination, somatic depressive symptoms, anxiety sensitivity, phobic anxiety and the specific combination of negative affectivity and social inhibition [15, 18–22]. Collectively these findings point to the likelihood that common processes underlying negative emotions generally also portend CVD risk [19], raising the possibility that an intervention that transcends diagnostic boundaries and targets core emotional processes would be a step toward improving mental health interventions among CVD populations.

### Limitations of the extant depression intervention findings in CVD

Several lines of evidence raise the possibility that interventions focusing solely on depression disorders have been ineffective in the population with CVDs. First, prior controlled efforts to address depression in patients with coronary artery disease [4, 23] and heart failure [24] via psychological and pharmacological interventions have reported only small, albeit significant, effects on depression symptoms. Strikingly, the effect sizes for depression symptom reduction are markedly smaller in CVD samples than that observed in other chronic diseases such as Type II diabetes samples [25]. Collective findings have prompted a closer examination of the specific therapeutic components of interventions for depression used in CVD samples that might lead to an improved outcome [26], as well as an exploration of novel methods of mental health service delivery such as collaborative care [27]. Intriguingly, neither avenue of empirical enquiry has consistently yielded moderate or larger effect sizes for depression symptom reduction to date. Likewise, despite initially promising findings from one collaborative care randomized controlled trial (RCT) suggesting a reduction in major adverse cardiac events (MACE) [28], these findings were not sustained in the longer term [23, 29]. Together, these findings point to the strong possibility that mental health interventions exclusively targeting depression in CVDs are incomplete and too narrow in focus.

### Anxiety burden and effects on CVD prognosis

Parallel to what has been reported for depression, an emerging literature has uncovered an association between anxiety with CVD morbidity [8, 15], prompting questions regarding whether depression is a discrete psychiatric risk factor for MACE [11, 15]. Specifically, two recent meta-analyses indicated that post-traumatic stress disorder was associated with a twofold recurrent acute coronary syndrome risk [7] whereas generalized anxiety disorder (GAD) was associated with a 21 % increase in MACE risk [15]. Although the association between panic disorder and CVD events is tenuous [9, 30–34], panic disorder nonetheless signifies high emergency department utilization for chest pain and diagnostic tests to rule out acute coronary syndromes [35], representing a major burden on the healthcare system.

### Importance of anxiety intervention in CVDs

Alongside depression, the American Heart Association [36] and the German Cardiac Society [21] recommend comprehensive assessment of anxiety disorders in CVD patients. In depressed CVD patients, the prevalence of comorbid anxiety disorders is 30 % to 50 % [15, 27]. In addition, 50 % of cardiac patients presenting for psychotherapy meet at least one anxiety disorder diagnosis [37, 38], and higher anxiety is associated with depression treatment resistance [39]. Despite the prevalence of anxiety disorders in CVDs exceeding community estimates [17] and comparable to depression prevalence in CVD [15], no clinical guidelines exist for treatment when anxiety disorder comorbidity is present in this population [40]. Moreover, with increasing recognition of the necessity to formulate interventions matching the complexity of CVD populations [37, 41] and the requirement for mental health interventions to match transdiagnostic developments in clinical psychology [42–47], the use of depression disorder-only treatments may become increasingly obsolete.

### Previous work supporting the need for a transdiagnostic approach in CVDs

Our recent work supports the assertion that an expansion of mental health interventions beyond depression to incorporate comorbid anxiety disorders is warranted in populations with CVDs. A screen-and-treat model of care for heart failure patients was undertaken in three South Australian tertiary hospitals where we observed that panic disorder and anxiety due to a medical condition was associated with high emergency department utilization [48]. Furthermore, a reduction in CVD readmissions was observed with CBT for GAD [49]. We hypothesized that an intervention focusing on somatic anxiety symptoms led to a significant reduction in CVD hospital readmissions and to an improved depression response [49].

Despite strong evidence collectively demonstrating how anxiety disorders are common and necessitate treatment in CVDs, a critical absence of interventions with broader reach beyond depression exists, which forms a major oversight in improving upon existing mental health interventions. Therefore, treatment of a broader range of emotional disorders and their common emotional processes likely would be an innovative step toward improving mental health interventions and cardiovascular health among CVD populations. Targeting the most common psychological processes that confer CVD risk with a single set of therapeutic principles would open the possibility for a more parsimonious application of effective mental health interventions to a broader range of CVD patients. Herein, we outline the methodology for a study of this type based on the unified protocol (UP) for transdiagnostic treatment of emotional disorders [42, 44–46].

## Methods

### Study design

This prospective study is a feasibility randomized controlled trial, of parallel design, comparing the effectiveness of the UP versus enhanced usual care. A total of 50 participants will be recruited from the Queen Elizabeth Hospital, a tertiary hospital in the western urban area of Adelaide, South Australia. Parallel to the main trial, a nonrandomized comparator cohort will be recruited comprising at least 150 persons scoring below the predetermined depression and anxiety severity thresholds. Figure 1 depicts the trial design. The trial will be conducted in accordance with the CONSORT statement [50].

**Fig 1 Fig1:**
[figure not shown]
Flow chart of CHAMPS participants through the study. CVD, cardiovascular disease; CHAMPS, Cardiovascular Health in Anxiety or Mood Problems Study; EUC, enhanced usual care; GAD-7, generalized anxiety disorder-7; MINI, MINI International Neuropsychiatric Interview; PHQ, Patient Health Questionnaire; UP, unified protocol

### Inclusion criteria

Inclusion criteria are as indicated below:Age ≥ 18 years.A primary hospital admission for CVD (specified by relevant International Classification of Disease codes for coronary artery disease, myocardial infarction, heart failure, atrial fibrillation, other ventricular or atrial arrhythmia, coronary revascularization intervention, symptomatic coronary heart disease including unstable angina pectoris, or heart valve disease).A MINI International Neuropsychiatric Interview (MINI) diagnosis by randomization naïve assessors of major depression, dysthymia, GAD, panic disorder, agoraphobia, social anxiety/phobia, or post-traumatic stress disorder.Above the severity threshold for depression PHQ scores (≥10) [51] or anxiety threshold GAD scores (≥7) [52].Fluency in English.

### Exclusion criteria

Exclusion criteria include the following:A psychosis or bipolar disorder diagnosis determined by medical history or randomization-naïve assessors.High suicide risk at psychiatric interview.Observed cognitive impairment or dementia impeding delivery of psychotherapy or ability to provide informed consent.Neurodegenerative condition (for example, Parkinson’s disease or multiple sclerosis)In receipt of GP, psychologist or psychiatrist counselling elsewhere.A diagnosis of drug and alcohol dependence or abuse determined by randomization-naïve assessors.Medical condition likely to be fatal within 1 year.

### Nonrandomized comparator cohort

Participants scoring below the depression and anxiety severity threshold on the PHQ-9 and GAD-7, and therefore those without any distress, will be part of a nonrandomized comparator cohort. The rationale for the comparator cohort is to answer empirical questions about EDBs, incident emotional disorders and trajectories of emotional distress. Several recent RCTs have adopted a similar approach and recruited a comparator cohort for observational purposes.

### Non-randomized comparator cohort eligibility

Age ≥ 18 years.A primary hospital admission for CVD (specified by relevant International Classification of Disease codes for coronary artery disease, myocardial infarction, heart failure, atrial fibrillation, other ventricular or atrial arrhythmia, coronary revascularization intervention, symptomatic coronary heart disease including unstable angina pectoris, or heart valve disease).Free from any MINI diagnosis by randomization-naïve assessors of major depression, dysthymia, GAD, panic disorder, agoraphobia, social anxiety/phobia, and post-traumatic stress disorder.Free from any MINI diagnosis by randomization-naïve assessors or medical history of psychosis or bipolar disorder.Below the severity threshold for depression PHQ scores (≤ 9) [51] or anxiety threshold GAD scores (≤ 6) [52].Fluency in English.

### Proposed sample

The proposed sample for this study was 50 patients randomized to the UP or EUC arm. Parallel to the RCT, 150 persons will be recruited into the nonrandomized comparator cohort. In the total sample (N = 200), incorporation of the nonrandomized comparator cohort (n = 150) and RCT participants (n = 50) will enable us to explore the rates of EDBs, physical activity, medication adherence, hospital readmission and feasibility of a screen-and-treat model of care.

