### Procedure

The potentially eligible patients are being identified at the hospital 1 to 4 days after their CVD admission by an authorized hospital staff member employed as a trial coordinator in the cardiology department. A pool of eligible participants will be determined by the trial coordinator’s review of cardiology admissions and medical records if required. In the first instance, persons will be approached on the hospital ward by the trial coordinator and provided with the study information sheet and an opportunity to discuss any aspects of the study with the trial coordinator. The potentially eligible patients are re-contacted by the study’s trial coordinator by letter and then telephone 2 to 8 weeks after their CVD admission. Eligible and consenting participants will provide written informed consent at the baseline appointment. Determination of the depression and anxiety thresholds will be made at baseline. Randomization and patient allocation to trial arms will take place by means of a random number generator prepared in advance by an independent statistician offsite. All participants undergo active monitoring for CVD events and mental well-being (PHQ-9 and GAD-7) through a scheduled phone call every 4 to 6 weeks after randomization. The numbers of eligible and successfully recruited patients will be monitored and discussed on a weekly basis between the CI and trial manager.

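### The N = 200 named for screen-and-treat feasibility is selected on screen and MINI result and filled to quotas, so it cannot show screening yield, false alarms or missed cases

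*Protocol article*

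**What the plan says.** The sample is named under Proposed sample: the cohort (150) and the trial participants (50) taken together, N = 200, "will enable us to explore the rates of EDBs, physical activity, medication adherence, hospital readmission and feasibility of a screen-and-treat model of care".

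Entry to each part depends on both the screen and the interview:

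- **Randomized trial (Inclusion criteria).** Patients need "A MINI International Neuropsychiatric Interview (MINI) diagnosis by randomization naïve assessors of major depression, dysthymia, GAD" or one of the other listed disorders. They must also be "Above the severity threshold for depression PHQ scores" (10 or more) or above the GAD-7 threshold (7 or more).
- **Cohort, eligibility list.** Patients must be "Free from any MINI diagnosis by" assessors of the same disorders, and have a PHQ score of 9 or less *or* a GAD score of 6 or less.
- **Cohort, narrative (Nonrandomized comparator cohort).** Patients score below threshold on the PHQ-9 *and* the GAD-7. The MINI is not mentioned.
- **Cohort, Study design.** The cohort is described as "comprising at least 150 persons scoring below the predetermined depression and anxiety severity thresholds". The Abstract likewise uses scores alone, but gives 150 without the words for a minimum.

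On timing, Procedure says: "Determination of the depression and anxiety thresholds will be made at baseline". Table 2 marks PHQ-9, GAD-7 and MINI in the eligibility column. Planned statistical analysis adds eligibility, acceptance and attrition rates, recruitment time and questionnaire compliance as feasibility measures.

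**The concern.** A screen-and-treat model starts from everyone who is screened. A later trial or service needs to know how many people screen positive, how many of those have a treatable disorder, and how many disorders fall below the cut-offs. The last matters here because the qualifying diagnoses include panic disorder, agoraphobia, social anxiety and post-traumatic stress disorder, whereas the two screening scales are described as measuring depression and generalized anxiety symptoms.

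The sample named for this question is formed after the screen and the MINI have been compared, and it retains mainly the people in whom they agree. Its ratio of distressed to non-distressed patients is set by recruitment targets. If feasibility is read from that sample, the workload from false alarms and the cases missed are largely or wholly out of view. Any rate of emotion-driven behaviors or readmission pooled over the 200 describes a mixture that the planners chose.

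**Working it through.** **Step 1. The plan's own figure.** 150 + 50 = 200, as stated. The randomized share is 50/200 = 25%, or less if the cohort exceeds 150. Both parts are recruitment targets, so the share is not an observed proportion.

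**Step 2. Every combination of results set against the entry rules.** For the cohort, the MINI rule of the eligibility list is combined first with the narrative's *and*, then with the list's literal *or*.

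| PHQ-9 ≥ 10 | GAD-7 ≥ 7 | MINI | Trial | Cohort (*and*) | Cohort (*or*) |
|---|---|---|---|---|---|
| no | no | negative | no | yes | yes |
| no | no | positive | no | no | no |
| no | yes | negative | no | no | yes |
| no | yes | positive | yes | no | no |
| yes | no | negative | no | no | yes |
| yes | no | positive | yes | no | no |
| yes | yes | negative | no | no | no |
| yes | yes | positive | yes | no | no |

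- With *and*, the trial takes 3 cells, the cohort 1, and 4 enter neither. Those 4 are the missed cases (one cell) and the false alarms (three cells).
- With the literal *or*, the two MINI-negative cells with one raised scale enter the cohort. Missed cases, and MINI-negative people raised on both scales, still enter neither group.

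**Step 3. Illustrative size.** Prevalence p, sensitivity Se and specificity Sp are not in the documents; all values below are assumptions.

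- Discordant share = p(1 − Se) + (1 − p)(1 − Sp)
- Positive predictive value (PPV) = p·Se / [p·Se + (1 − p)(1 − Sp)]

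| p | Se / Sp | Discordant share | PPV |
|---|---|---|---|
| 0.25 | 0.80 / 0.85 | 0.050 + 0.1125 = 16% | 0.20/0.3125 = 0.64 |
| 0.25 | 0.90 / 0.90 | 0.025 + 0.075 = 10% | 0.225/0.30 = 0.75 |
| 0.25 | 0.70 / 0.75 | 0.075 + 0.1875 = 26% | 0.175/0.3625 = 0.48 |

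With p from 0.20 to 0.40 and Se/Sp of 0.70/0.75, 0.80/0.80 and 0.90/0.90, the discordant share runs from 10% to 27%, PPV from 0.41 to 0.86, and negative predictive value from 0.79 to 0.97.

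In the first row, 50 concordant positives need 50/(0.25 × 0.80) = 250 assessments. These would include 250 × 0.1125 ≈ 28 false alarms and 250 × 0.05 ≈ 12 missed cases. Exclusions and refusals are ignored, so the real number assessed would be larger.

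**Step 4. Yield.** Screen-positive share = p·Se + (1 − p)(1 − Sp). The first row gives 0.20 + 0.1125 = 31%. Over the wider grid it runs from 0.18 + 0.08 = 26% (p 0.20, 0.90/0.90) to 0.32 + 0.12 = 44% (p 0.40, 0.80/0.80). The targets give about 25% under *and*, whatever the true value.

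**Step 5. What the literal *or* changes.** Let q be the fraction of false alarms raised on one scale only. Expected false alarms among the 150 = 150 × q(1 − Sp)/[q(1 − Sp) + Sp]; prevalence cancels. With q = 0.25 and Sp = 0.90 this is 150 × 0.025/0.925 ≈ 4. With q = 0.75 and Sp = 0.75 it is 150 × 0.1875/0.9375 = 30. The cohort's make-up therefore depends on which description is followed.

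**The case against.** The strongest reply is that the plan never offers a diagnostic accuracy study. It speaks of exploring feasibility, and no section proposes sensitivity, specificity or predictive values. A reader might infer that the trial will present screening as error-free, with 100% sensitivity and predictive value. The documents do not support that: no such figure is planned, and under the eligibility list's literal *or* the cohort would contain some false alarms. This part of the reply stands in full.

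Second, Planned statistical analysis includes eligibility and acceptance rates, whose natural denominator is the people screened. That covers part of the gap. It does not say that people entering neither group will be counted by screen and MINI result, and Proposed sample still ties the screen-and-treat question to the 200.

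Third, a reader might infer that discordant people have no route at all. That cannot be established: the flow chart (Figure 1) is not shown, and being ineligible for both groups is an ordinary screening outcome.

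Fourth, the article does not say that one pooled rate will be reported. The total-sample analyses it describes are associations with readmission and multilevel trajectory models, which a 25:75 mix does not in itself invalidate. The caution about rates applies only if they are pooled.

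Finally, the cohort definitions in the Abstract, Study design and the narrative section use scores alone. Read by themselves, they would let missed cases into the cohort. The exclusion of missed cases therefore rests on the eligibility list, which is the most specific statement of entry.

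**Conclusion.** The point holds as a limit on interpretation. Under the two eligibility lists, people with a MINI diagnosis and sub-threshold scores are outside the 200. MINI-negative people above threshold are outside it wholly (narrative *and*) or in part (literal *or*). With the group sizes set by targets, the 200 cannot show screening yield, false alarms or missed cases, and a pooled rate would carry the recruitment mix.

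This conclusion follows from the entry rules and needs no assumed figure. Its size does. Under the assumed ranges, 10% to 27% of people assessed would be discordant, but the documents supply no prevalence or screening accuracy, so these numbers are illustrative only. The correction is worth making because the trial's purpose is to inform a larger one and the needed data are already collected at eligibility.

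**What to change.** 1. **Proposed sample:** take screen-and-treat feasibility out of the 200 and assess it in all consenting people who complete the baseline PHQ-9, GAD-7 and MINI. This agrees with the eligibility rates already planned.
2. **Reporting:** give the screen-by-MINI table for that set, including those who enter neither group.
3. **Rates:** report emotion-driven behaviors and readmission separately for the trial and the cohort, or weight them to the screened proportions. Weighting can correct the mix of the enrolled groups; it cannot supply follow-up for people who were not enrolled.
4. **Definitions:** reconcile the cohort's description across the Abstract, Study design, the narrative section and the eligibility list. This includes the role of the MINI and the *and* against the *or*. The eligibility list should not simply be copied into the other sections as it stands, because that would spread the *or*.

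The cost is a change of wording and one table from data already collected. The small downside is that consent must cover keeping the baseline data of people enrolled in neither group. As the trial is already recruiting, whether the existing consent does so should be checked before their data are used.

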### Planned statistical analysis

Data management is outlined elsewhere in our protocol. Comparisons between UP, EUC and the nonrandomized comparator cohort will be made at each follow-up time point on patient level of satisfaction with aspects of psychosocial care. We will evaluate whether screening, education, and support in EUC is a suitable alternative to UP. We will also monitor linkages with primary care to determine whether our suicide risk management strategy is viable when routine depression screening is implemented. These data will help inform the design and day-to-day running of a larger more definitive RCT. In terms of feasibility, we will also evaluate the recruitment eligibility, acceptance, and attrition rates, the length of time taken to recruit, and compliance with the psychosocial questionnaire battery.

In the total sample, incorporating the nonrandomized comparator cohort, the association between EDBs, physical activity, and medication adherence with readmission will be examined. Incident psychological distress and distress trajectories will be evaluated in multi-level models to provide a snapshot of different distress trajectories on each of the measures used in CHAMPS. The longitudinal changes in QOL will also be analyzed in the same manner as incident psychological distress and distress trajectories described above.

